2  
3 **PRINCIPAL INVESTIGATORS:** [name] MS, [name] MS

4 **PROTOCOL TITLE:** Studying the PhilAdelphia Resilience Project as a Response to Overdose  
5 (SPARROw)

6  
7 **1. INTRODUCTION AND PURPOSE:**

8  
9 **1.1. Objectives:** The objective of this proposal is to evaluate the effectiveness and  
10 implementation of two City of Philadelphia Resilience Project programs to reduce  
11 opioid overdose: (1) the Alternative Response 2 (AR2) that accompanies ambulances  
12 responding to overdoses and aims to deliver harm reduction and care linkage to people  
13 who refuse hospital transport, and (2) blight remediation of abandoned buildings and  
14 land. This application leverages a natural experiment within the Resilience Project  
15 implementation to evaluate its impact on overdose outcomes.

16  
17 We propose to address the following Specific Aims:

18  
19 **SA1: Determine the effectiveness of the Resilience Project AR2 on opioid overdose**  
20 **outcomes for EMS patients who refuse hospital transport after overdose.** Using a  
21 quasi-experimental design, we will compare the proximal overdose outcomes (rates and  
22 timing of treatment linkage) and distal overdose outcomes (non-fatal overdoses within  
23 60 days and overdose deaths within 24 months) for patients who receive AR2  
24 engagement compared to those who, due to timing or location restrictions, receive  
25 traditional EMS care alone.

26  
27 **SA2: Evaluate the impact of Resilience Project blight remediation activities on**  
28 **fatal and non-fatal opioid overdose.** Blight remediation activities vary across time and  
29 space in Kensington. We will use a difference-in-difference design to compare fatal and  
30 non-fatal overdoses in the 60 days before and after any given remediation effort  
31 compared to the same time period in two nearby locations that did not get remediated  
32 but had comparable pre-blight remediation overdose rates. We will select one control  
33 location from within Kensington and one just outside the Resilience Project geographic  
34 boundary.

35  
36 **SA3: Evaluate implementation of the Resilience Project by a) characterizing the**  
37 **fidelity of the AR2 intervention in Kensington, b) measuring factors that moderate**  
38 **AR2 fidelity, including blight, c) assessing barriers and facilitators to AR2**  
39 **implementation, and d) determining the costs for AR2 and blight remediation**  
40 **interventions.** We will characterize AR2 fidelity by measuring which components are  
41 completed at each engagement (take-home naloxone, rapid treatment referral,  
42 transportation to treatment, family engagement, phone number acquisition, and/or phone  
43 follow-up). We will measure potential moderating factors including nearby blight at  
44 AR2 engagement locations and AR2 team composition. We will assess barriers and

facilitators to AR2 fidelity with interviews. Last, we will determine the costs for AR2 and blight remediation to inform sustainability and dissemination.

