## 1.2. Background:

The opioid crisis has hit Philadelphia particularly hard, with over 46 overdose deaths per 100,000 residents in 2017, twice the national average. In response, the City of Philadelphia developed an overarching prevention strategy, the Resilience Project, which includes both services targeted toward people who use opioids and neighborhood environment interventions that address the blighted conditions where most overdoses occur. The Resilience Project focuses on Kensington, the neighborhood with the city's highest overdose rate and high rates of poverty, homelessness, and dilapidated neighborhood conditions

Experiencing an overdose often brings people who use opioids into contact with healthcare providers and represents an opportunity to improve outcomes through harm reduction and care linkage. For example, many people are brought to Emergency Departments after overdose and are linked to care through "warm hand off" programs. However, among the 15,000 annual emergency medical services (EMS) calls in Philadelphia for overdose, up to 28% of patients refuse transport to the hospital and are, thus, at acute risk of later overdose. The Resilience Project AR2 aims to close this gap by engaging people who use opioids at the *time and place* of their overdose. The AR2 is a mobile medical unit – staffed with a social worker and paramedic – that accompanies ambulances responding to overdose calls in Kensington to engage in treatment or distribute naloxone to patients who refuse hospital transport.

Another Resilience Project program is blight remediation. The places where people live, work, and play are significant drivers of health. This is particularly important in the opioid epidemic, as blighted neighborhood conditions are associated with drug sales, substance use, and morbidity. Resilience Project blight remediation efforts include abatement of vacant lots and cleaning and sealing of abandoned houses. Changing the neighborhood context of high-risk overdose *places* such as Kensington could be an innovative method to augment opioid overdose prevention efforts, including the AR2.

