- b. **Paired encounter analysis.** For the analysis of paired encounters (one AR2 and a non-AR2 occurring while the AR2 was on another call), we will use an exact McNemar's test for paired data for 0/1 outcomes (death, relapse) and a Cox proportional hazards model for paired data for censored time to event outcomes (time to treatment linkage, time to subsequent overdose). For each AR2 encounter we try to identify a non-AR2 encounter at the same time period within the AR2 response zone. If we find one, these pair of encounters are labeled as a pair and we will follow the patients for 60 days for linkage and non-fatal overdose, and 24 months for fatal overdose, and record outcomes. If multiple non-AR2 encounters happen simultaneously, then conditional logistic regression and stratified Cox models will extend the analysis from a 1-to-1 pairing to a 1-to-many matching. For our power calculations we assume a 1-to-1 pairing, a one-sided test for a reduction in adverse outcomes with  $\alpha = 0.05$  and a power level of at least 0.80. To detect a 50% reduction in the death rate attributable to the AR2 (assumed reduction from 10% to 5%), we need 370 pairs of encounters. To detect a 50% reduction in the rate of repeat non-fatal overdoses (from 30% to 15%), we need 105 pairs of encounters. To detect a 50% reduction in the hazard rate of time to subsequent overdose (equivalent to roughly 19% having a subsequent overdose within one year to 9.5%), we need 200 pairs of encounters. To detect an increase of 50% in the odds of seeking treatment within 60 days of an overdose (from 26% seeking drug treatment after an overdose within 60 days to 35% with AR2), we need 360 pairs of encounters.

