## **AIM 2 Analysis:**

- a. **Analysis plan and power calculation.** We will analyze separately abandoned home remediation and vacant lot abatement, but both will have a similar analysis structure. We will use a conditional Poisson regression model of the form  $\log(E(\text{count})) = \beta_0 + \beta_1 \text{clean} + \beta_2 \text{post} + \beta_3 \text{clean} \times \text{post}$ , where clean is a 0/1 indicator of whether the location went through blight remediation and post is a 0/1 indicator of whether the time period measured is post-blight remediation in the treated location. The conditional Poisson model accounts for the matched pairs of location.  $\exp(\beta_3)$  is of

primary interest, a ratio of rate-ratios, contrasting the relative change in overdose rates in the treated area pre- versus post-remediation with the relative change in overdose rates in the comparison locations.

We anticipate at least 55 blight remediated locations with which we can pair with 55 un-remediated locations. The average buffer area will have 1.2 overdoses per month. Under such circumstances we will be able to detect reductions of 50% or more in overdose rates with power 0.80.

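### Aim 2 rests on one 60-day pre-window and a two-period model, so the planned analysis has no parallel-trends check and cannot show whether sites were at a temporary peak just before remediation

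*Protocol*

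**What the plan says.** Protocol 1.1 (SA2) sets the Aim 2 contrast as fatal and "non-fatal overdoses in the 60 days before and after any given remediation effort", set against the same period at two nearby unremediated locations. The same sentence says that those locations had comparable overdose rates before remediation, without giving a look-back window.

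Protocol 5.5 (AIM 2 Analysis) writes out the conditional Poisson model with terms for clean, post and clean × post, where "post is a 0/1 indicator of whether the time period measured is post-blight remediation in the treated location". The interaction, exp(β3), is of "primary interest, a ratio of rate-ratios". No other pre-period, lead term or longer baseline is stated for Aim 2.

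The sizing inputs are in the same section. At least 55 treated sites are expected, each with one untreated partner. The event rate is given as "The average buffer area will have 1.2 overdoses per month", and the claim made from these inputs is that "we will be able to detect reductions of 50% or more in overdose rates with power 0.80".

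Protocol 3.1 (AIM 2, Comparator Group) selects control block groups on sociodemographic profile. It does not name overdose rates. It asks only that a control was eligible and had no remediation in the preceding 30 days.

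**The concern.** City agencies, not a random process, decide which houses and lots are remediated and when. Protocol 1.2 describes the program as "neighborhood environment interventions that address the blighted conditions where most overdoses occur", but the protocol does not say what prompts work at a given site on a given date. If some of the work follows a recent run of overdoses, the 60 days before it are a chance high that would fall back anyway. Controls chosen on sociodemographic profile would not share that high, and the interaction would record the fall as benefit.

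A difference-in-differences estimate depends on treated and control locations moving in parallel without the intervention. With one pre-period and one post-period, the data that enter the model cannot test this. The stake is the main Aim 2 estimate, and also the interim blight results, which Protocol 6.8 plans to share with City partners to inform prevention work.

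**Working it through.** **Inputs.** 55 treated and 55 control locations, 1.2 overdoses per month (5.5); 60-day windows, taken as 2 months (1.1). Expected events per location per window: 1.2 × 2 = 2.4. Expected events per arm per window: 55 × 2.4 = 132. Aim 2 states no alpha or sidedness. Aim 1 specifies "a one-sided test for a reduction in adverse outcomes with" α = 0.05, so one-sided 0.05 is used here and two-sided is shown where it matters.

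**The protocol's own power figure.** For a 50% reduction, with four Poisson cells:

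- Var = 1/132 + 1/(132 × 0.5) + 1/132 + 1/132 = 5/132, so SE = 0.195.
- Power = Φ(ln 2/0.195 − 1.645) = 0.97 one-sided, or 0.945 two-sided. The stated 0.80 is not reproduced.
- With 1-month windows, SE = √(5/66) = 0.275 and power is 0.81 one-sided, close to the stated figure. Overdispersion of about 2.05 (one-sided) or 1.6 (two-sided) at 60 days would also give 0.80.

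The window behind the power statement should therefore be reconciled with SA2. For the present point, the result shows that on Poisson inputs the 60-day design is not short of power for its own target.

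**How noisy the baseline is.** For a Poisson count with mean 2.4, P(3 or more) = 0.43 and P(5 or more) = 0.096, with no change in underlying risk.

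**False fall if timing follows recent counts.** Assumptions: constant rate of 2.4 per window, no true effect, controls not matched on overdose counts.

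- Mean pre-count given 3 or more events: 2.4 × P(X ≥ 2)/P(X ≥ 3) = 2.4 × 0.692/0.430 = 3.86.
- All sites triggered: ratio = 2.4/3.86 = 0.62, a 38% fall.
- A quarter of sites triggered: mean pre-count = 0.25 × 3.86 + 0.75 × 2.4 = 2.76; ratio = 2.4/2.76 = 0.87, a 13% fall. In 4,000 simulated trials of 55 pairs, the one-sided false-positive rate was about 21% against a nominal 5%.
- No sites triggered: ratio 1, no bias.

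Lasting differences in rate between sites reduce the bias. If every site is triggered at 3 or 4 or more events, a gamma spread of rates gives a fall of 16–18% (shape 1), 22–26% (shape 2) or 29–36% (shape 5), against 38–49% with no spread.

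**Would matching on overdose counts settle it?** If controls are matched on the same 60-day count and all locations share one rate, the simulated ratio is 1.00 and false positives do not rise. If underlying rates differ, matching creates its own bias. Assume gamma shape 2, treated mean 2.4 and control-population mean 1.6. Controls matched to a mean count of 2.4 then have an expected next-window count of 1.6 × (2 + 2.4)/(2 + 1.6) = 1.96. That is a fall of about 19% with no intervention, and a ratio of 2.4/1.96 ≈ 1.23, which would mask a benefit.

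**Effect of a longer baseline** (k pre-windows, 60-day post-window, no effect): SE = √(2/(132k) + 2/132).

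- k = 1: 0.174. k = 6: 0.133. k = 5 (12 months without the adjacent window): 0.135.
- The detectable reduction r at power 0.80 solves −ln(1 − r) = 2.486 × √(2/(132k) + 1/132 + 1/(132(1 − r))). It is 37% for k = 1 and about 31% for k = 5.
- A 12-month baseline that keeps the trigger window still gives a ratio of 2.4/((3.86 + 5 × 2.4)/6) = 0.91 when all sites are triggered at 3 or more. Omitting that window removes the bias under the stated assumption.

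**The case against.** The strongest reply is that SA2 already answers the concern, because controls are said to have had comparable overdose rates before remediation. The clause is relevant and would help if it were carried out on the same window. However, the selection procedure in 3.1 does not carry it out, and matching on a noisy 60-day count can bias the estimate in the other direction.

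Second, no passage says that remediation is prompted by overdoses. The description in 1.2 is of the neighborhood program, not of the choice of a house or a date. The outcome is also counted over a buffer area, so a trigger at one address need not select on the buffer's total. This stands. A reader might infer that exp(β3) will show a spurious benefit, but the documents do not support that; they leave it open.

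Third, a reader might infer that the short baseline leaves Aim 2 underpowered. It does not on the protocol's Poisson inputs, as shown above.

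Fourth, lead terms and sensitivity baselines are often left to an analysis plan, and a short local window is defensible because a longer one takes in more of the other Resilience Project activity. Both points have weight. The single pre-window and the two-period model are nevertheless stated choices, and the absence of a trend check follows from them. It does not follow from a lack of data: Protocol 2.4 plans two years of administrative records, so a check is feasible for many sites.

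**Conclusion.** The concern holds in a conditional form. The analysis as stated contains no check of parallel trends and cannot distinguish a remediation effect from a return to normal after a temporary peak. The possible false fall is about 13% if a quarter of sites are triggered at 3 or more events and 38% if all are. Both figures assume a constant rate, no true effect and controls not matched on the same window. The bias is smaller where sites differ lastingly in rate, and zero if timing is unrelated to recent counts. Which case applies cannot be read from the protocol, and the planned model would not reveal it. SA2 and 3.1 disagree on how controls are chosen and must be reconciled. The precision gain from a longer baseline is a side benefit.

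**What to change.** 1. Keep the 60-day before/after contrast as the main estimate.
2. Extract earlier consecutive 60-day pre-windows, up to 12 months where City EMS and Medical Examiner records allow, for treated and comparator locations.
3. Fit the same conditional Poisson model with period indicators and report the clean-by-pre-period terms, with a joint test, as the parallel-trends check.
4. Pre-specify a sensitivity estimate on the longer baseline without the window directly before remediation.
5. State one control-selection rule in SA2 and 3.1. If overdose rates are part of it, give the look-back window. Require controls to be unremediated over the baseline used.
6. Record what is known about how the City chooses sites and dates.

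The cost is a wording change and a longer extract of records that the City already holds. Sites remediated early will have a shorter baseline, and fewer comparators will have stayed unremediated throughout. A longer baseline is also more exposed to other Resilience Project activity, particularly in the comparison with locations outside Kensington. That exposure is a reason to use it as a sensitivity analysis and not as the main estimate. Leaving out one window removes the bias only if the run-up is confined to those 60 days; the pre-period terms would help to show whether it is.

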## 1.2. Background:

The opioid crisis has hit Philadelphia particularly hard, with over 46 overdose deaths per 100,000 residents in 2017, twice the national average. In response, the City of Philadelphia developed an overarching prevention strategy, the Resilience Project, which includes both services targeted toward people who use opioids and neighborhood environment interventions that address the blighted conditions where most overdoses occur. The Resilience Project focuses on Kensington, the neighborhood with the city's highest overdose rate and high rates of poverty, homelessness, and dilapidated neighborhood conditions

Experiencing an overdose often brings people who use opioids into contact with healthcare providers and represents an opportunity to improve outcomes through harm reduction and care linkage. For example, many people are brought to Emergency Departments after overdose and are linked to care through "warm hand off" programs. However, among the 15,000 annual emergency medical services (EMS) calls in Philadelphia for overdose, up to 28% of patients refuse transport to the hospital and are, thus, at acute risk of later overdose. The Resilience Project AR2 aims to close this gap by engaging people who use opioids at the *time and place* of their overdose. The AR2 is a mobile medical unit – staffed with a social worker and paramedic – that accompanies ambulances responding to overdose calls in Kensington to engage in treatment or distribute naloxone to patients who refuse hospital transport.

Another Resilience Project program is blight remediation. The places where people live, work, and play are significant drivers of health. This is particularly important in the opioid epidemic, as blighted neighborhood conditions are associated with drug sales, substance use, and morbidity. Resilience Project blight remediation efforts include abatement of vacant lots and cleaning and sealing of abandoned houses. Changing the neighborhood context of high-risk overdose *places* such as Kensington could be an innovative method to augment opioid overdose prevention efforts, including the AR2.

This application leverages a natural experiment within the implementation of the Resilience Project to evaluate its impact on fatal and nonfatal opioid overdose. We hypothesize that interventions targeted at the *time and place* of opioid overdose – including the AR2 and blight remediation efforts – will be more effective at preventing overdose compared to standard EMS care or absence of environmental modifications.

## 2. CHARACTERISTICS OF THE STUDY POPULATION:

**2.1. Target population and Accrual:** Our target population are all people who have an opioid overdose in the Kensington neighborhood of Philadelphia, PA and surrounding areas. We are not enrolling people directly. Rather, we will be analyzing data from the

City of Philadelphia for people who meet our criteria. There are two primary ways in which a person may be part of our study – if they interact with the Alternative Response Unit (AR2) or traditional EMS care after an overdose. We will also look at all overdose deaths in this neighborhood. Of note, the intent of this project is to study opioid overdoses in Kensington; however, due to the nature of drug overdoses and the fact that many people use multiple substances, we recognize that often times it will be difficult or impossible to determine if the overdose was due to opioids. Therefore, we will be including encounters for all overdoses in our study.

## **2.2. Key Inclusion Criteria:**

**Inclusion criteria for the intervention group include all AR2 encounters where:**

- The encounter is for a presumed overdose
- Patients are at least 18 years of age
- Located within the Kensington area (AR2 dispatch zone)
- From May 1, 2019 to April 30, 2021 (24 months)

**Inclusion criteria for the comparator group include all EMS encounters where:**

- The encounter is for a presumed overdose
- Patients are at least 18 years of age
- Located within the Kensington area (AR2 dispatch zone) and areas that are immediately adjacent
- From May 1, 2019 to April 30, 2021 (24 months)

## **2.3. Key Exclusion Criteria:**

**Exclusion criteria for the intervention group:**

- Encounters for children younger than 18
- Encounters subsequently deemed non-overdose related
- Encounters where the patient is pronounced dead at scene
- Repeat encounter for a patient previously encountered during the study period

**Exclusion criteria for the comparator group:**

- EMS encounters for children younger than 18
- EMS encounters subsequently deemed non-overdose related
- EMS encounters where the patient is pronounced dead at scene
- Repeat EMS encounter for a patient previously encountered during the study period

Additionally, another part of the study will involve interviewing the AR2 team. We define the AR2 team as any individual involved in the creation and management of AR2, including direct AR2 staff members, leadership, and AR2 adjacent staff such as EMS workers who may interact with the AR2– we will aim to interview all such individuals (n = 40 people).

## **2.4. Subject Recruitment and Screening:** For people who interact with the AR2 or traditional EMS, we will not be doing any specific recruitment to the study. The

population will be added to our study retrospectively and followed using city administrative data. Sources of research material consist primarily of administrative data already collected by the City of Philadelphia including information about all AR2 encounters, EMS data regarding non-fatal opioid overdose dispatches, Medical Examiner data regarding fatal opioid overdoses, and Department of Behavioral Health data regarding substance abuse treatment. We will collect data over a 2-year time period.

We will recruit AR2 team members to participate in semi-structured qualitative interviews through talking with them directly about the study. We will not be recruiting AR2 team members via flyers or posters. We will rely on a snowball sampling technique, where AR2 team members that we speak with directly are able to refer to us other individuals they believe would be eligible to be interviewed.

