- The ARU delivers six core services on scene to patients who refuse transport to the hospital: 1) dispensing of take-home naloxone, 2) referral to a treatment facility that has immediate availability and can provide MAT, 3) transportation to the facility, 4) family engagement, 5) acquisition of patient telephone information for follow-up, and 6) connect over the phone with the patient in follow-up. If the ARU vehicle arrives after the ambulance, ARU staff provide backup support focused on harm reduction and linkage to care as needed. ARU interventions can occur whether or not naloxone has been administered. These services are, in other settings, limited to hospital-based and fixed community-based sites and are largely outside of the scope of traditional EMS care. While EMS has the capacity to provide take-home doses of naloxone (depending on availability), anecdotally uptake has been low in Philadelphia. Moreover, traditional EMS does not have the capacity to refer patients to treatment programs, provide transportation directly to treatment programs, or follow up with people who have experienced overdose. These patients, many of who are revived by naloxone, are at particularly high risk of repeat overdose and death and do not typically have access to harm reduction or OUD treatment in locations where they live and/or use drugs. Based on total EMS encounters for overdose in Philadelphia -- including those that receive naloxone and those that don't -- and our knowledge of EMS transport refusal rates in Kensington (approximately 25%-30%), we estimate between 300 and 500 ARU engagements per year, or 600-1000 engagements over our two-year study period.

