- b. **Characterize which AR2 components are completed (fidelity).** First, we will use the established AR2 database to characterize which AR2 dispatches result in: 1) dispensation of take-home naloxone, 2) referral to a treatment facility that has immediate availability and can provide MAT, 3) transportation to a treatment facility, 4) family engagement, 5) collection of patient telephone information, and 6) telephone follow up within 7 days of encounter. Last, we will characterize which AR2 dispatches lead to any interaction with the individual who experienced the overdose (as some persons leave the scene after being administered naloxone by police, EMS, or a bystander). AR2 staff record each of these variables in real-time for each AR2 dispatch. Data are imported into a secure database and stored at Philadelphia Fire Department headquarters.

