**4.4. Administration of Surveys and/or Process:**

**Process for Review of Databases:** We will use data from four different City of Philadelphia departments: Philadelphia Department of Public Health (PDPH), Philadelphia Fire Department (PFD), Department of Behavioral Health and Intellectual disAbilities, and Managing Director's Office (MDO). These data are not currently linked between departments (we have letters of support from each agency). AR2: the AR2 dispatch and encounter data will be shared from both the PDPH and PFD databases. These data include 1) date, time, and location for all AR2 interactions, 2) demographic information about each participant including name and date of birth, and home address (when available), and 3) information about which components of the AR2 intervention were delivered during each engagement and in follow up.

Data related to linkage to care outcomes will be extracted from the DBHIDS Enterprise Data Warehouse. This data system includes all Medicaid plus uninsured claims for substance abuse treatment and care in Philadelphia. There is robust Medicaid penetration among opioid users in Philadelphia. In 2017, there were over 15,000 unique beneficiaries with opioid use disorder using behavioral health services, up from 9,000 in 2010. DBHIDS has committed to sharing these data in a manner that can be linked to EMS and

AR2 visit. This ensures that we will be able to track the substantial number of people who use opioids and who remain in Philadelphia through the behavioral health system after they have come into contact with the AR2 or EMS.

Data regarding fatal opioid overdose will come from the PDPH through the Philadelphia Office of the Medical Examiner, which sits within the PDPH. These data will include the name, date of birth, and death location for all fatal opioid overdose victims. The second distal outcome is non-fatal overdose, data which will come from both the PFD and the PDPH. The PFD will provide data for all EMS overdose related encounters, including date, time, and location of the dispatch; patient name and date of birth; patient home address (when available); and outcome of encounter (refused transport vs. transport to a hospital).

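### The only non-fatal overdose data the protocol describes are EMS records, while the AR2 hands out naloxone that may keep a repeat overdose out of those records; the outcome and the claim should be limited to EMS-attended overdose

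*Protocol*

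**What the plan says.** **Outcome source.** Protocol 2.4 lists "EMS data regarding non-fatal opioid overdose dispatches" among the administrative sources. Section 4.4 says: "The second distal outcome is non-fatal overdose, data which will come from both the PFD and the PDPH". The content it then describes is the fire department's: "The PFD will provide data for all EMS overdose related encounters". What the health department (PDPH) contributes to this outcome is not described.

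**Intervention.** In 3.1, Aim 1, item c, the first of the six core services is "1) dispensing of take-home naloxone". The same item says that EMS can also supply take-home doses, but that "anecdotally uptake has been low in Philadelphia". Item a of the same aim adds that people who refuse transport typically do not get take-home naloxone at the time of the event.

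**Follow-up and test.** Section 5.5, Aim 1, item b follows each pair for "60 days for linkage and non-fatal overdose, and 24 months for fatal overdose" and sizes the study with "a one-sided test for a reduction in adverse outcomes" at alpha 0.05. Item a follows patients to a subsequent overdose or death.

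**Reading of the result.** The hypothesis at the end of 1.2 is that the interventions prevent overdose better than standard EMS care does. The framework in 3.1, Aim 1, item a likewise expects fewer non-fatal and fatal overdoses.

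**The concern.** An overdose reversed by a companion with a take-home kit and no 9-1-1 call leaves no trace in EMS records. If AR2 patients hold more kits, a repeat overdose has a lower chance of being recorded in the AR2 arm, and the intervention is the cause. This is differential outcome detection, not confounding.

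The Aim 1 designs in 5.5 address something else. Pairing on time and place, propensity reweighting and the difference-in-difference all make patients comparable at the encounter. None acts on detection that the intervention alters afterwards. The difference-in-difference subtracts a time-of-day contrast from an area without the AR2, where this change in detection does not occur.

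Two outcomes are exposed: the 60-day non-fatal overdose rate and the time to subsequent overdose, in which a patient with an unseen overdose stays at risk as event-free. Deaths come from the Medical Examiner and treatment linkage from behavioral health claims, so neither needs a repeat EMS call to be recorded.

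A misreading would have consequences. Section 6.8 sends half-way results to the City to inform prevention, and 3.1, Aim 1, item c ties longer AR2 hours to a finding of effectiveness.

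**Working it through.** **Inputs from 5.5, Aim 1, item b:** repeat non-fatal overdose 30% in the comparator and 15% with the AR2; 105 pairs; exact McNemar test; one-sided alpha 0.05; power at least 0.80.

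**Input not in the protocol:** f, defined below.

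**Step 1: reproduce the protocol's figure.** With independent members of a pair, comparator rate p0 and AR2 rate p1:
- pairs with an event only in the comparator: p0(1 − p1) = 0.30 × 0.85 = 0.255
- pairs with an event only in the AR2 member: p1(1 − p0) = 0.15 × 0.70 = 0.105
- discordant share: 0.255 + 0.105 = 0.360
- among discordant pairs, share favouring the AR2: 0.255 / 0.360 = 0.708

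Summing the exact one-sided binomial rejection probability over the number of discordant pairs gives power 0.798 at 105 pairs and 0.805 at 107. The protocol's 105 is reproduced; its arithmetic is not at issue.

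**Step 2: define the detection gap.** Let a0 and a1 be the shares of repeat overdoses that reach EMS records in the comparator and AR2 arms. Then

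recorded risk ratio = true risk ratio × (a1 / a0) = true risk ratio × (1 − f), with f = 1 − a1/a0.

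Only the excess loss in the AR2 arm enters; under-recording common to both arms cancels from the ratio. I treat 30% as the recorded comparator rate and count at most one overdose per patient in the window. A patient with a second, recorded overdose would still count as an event, which would weaken the effect of f.

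**Step 3: set the true effect to zero.** The recorded AR2 rate is 0.30 × (1 − f). The calculation of step 1 at 105 pairs then gives:

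| f | recorded AR2 rate | discordant pairs favouring AR2 | probability of declaring a reduction |
|---|---|---|---|
| 0 | 30.0% | 0.500 | 0.037 |
| 0.03 | 29.1% | 0.511 | 0.050 |
| 0.05 | 28.5% | 0.518 | 0.061 |
| 0.1 | 27.0% | 0.537 | 0.095 |
| 0.2 | 24.0% | 0.576 | 0.208 |
| 0.3 | 21.0% | 0.617 | 0.384 |
| 0.5 | 15.0% | 0.708 | 0.798 |

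At f = 0 the exact test is conservative, hence 0.037 and not 0.05. At f = 0.5 the gap alone reproduces the whole planned effect of 30% to 15%. The bias is a fixed ratio, so a larger sample does not reduce it.

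**Step 4: what small f looks like.** Not every AR2 patient receives a kit, and not every kit replaces a 9-1-1 call. If 30% receive one and 10% of their overdoses then go unattended, f = 0.30 × 0.10 = 0.03. With 50% and 10%, f = 0.05. These shares are my assumptions.

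**Step 5: tipping point.** For an observed recorded risk ratio R, the excess that explains it entirely is f* = 1 − R. For example, R = 0.5 needs f* = 0.5.

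**The case against.** The strongest reply is that the size and even the net direction are unproven.

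- **Source.** A reader might infer that a repeat overdose is counted only when EMS is called. The protocol does not support *only*: 4.4 names the health department as a second source and leaves its content open. That gap has to be closed before the concern can be sized.
- **Direction.** A reader might conclude that the results must be biased towards the AR2. Opposite forces exist: naloxone can turn a death into a recorded non-fatal overdose, and AR2 contact could make a later 9-1-1 call more likely. This one mechanism favours the AR2; the sum of all of them is not known.
- **Bystander reversals.** It is tempting to cite 3.1, Aim 3, item b, which notes that "some persons leave the scene after being administered naloxone by police, EMS, or a bystander". That text describes AR2 dispatches, where an overdose call had already been made. It does not show reversals that EMS never sees.
- **Naloxone contrast.** EMS can also dispense kits, and the statement of low uptake is anecdotal. Item a of Aim 1 points the same way, but no figure is given for either arm.
- **Magnitude.** f has no source. At 0.03 to 0.05 the false-positive probability is only 0.050 to 0.061, close to nominal.
- **Place for the fix.** Sensitivity analyses usually belong in a statistical analysis plan, which is not at hand, so the lack of one here is no fault in itself.

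All six points stand as limits on what can be said. They do not remove the core: the protocol itself fixes the described data source and the reading of the result as prevention, and no Aim 1 design can separate fewer overdoses from fewer EMS-recorded overdoses.

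Nor can deaths settle the matter. Naloxone can lower deaths without lowering how often people overdose, so a fall in deaths is compatible with the very artefact at issue.

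**Conclusion.** The concern holds as a limit on ascertainment and interpretation. From the data the protocol describes, a lower recorded rate or a longer recorded time to overdose in the AR2 arm could reflect fewer overdoses, fewer EMS contacts per overdose, or both. Under no true effect and the assumptions of steps 2 and 3, the chance of a false reduction at 105 pairs runs from 0.061 at f = 0.05 to 0.384 at f = 0.3. It is near nominal if f is about 0.03. The results assume independent pair members, a 30% recorded comparator rate and no opposing mechanism. I did not compute a corresponding figure for the time-to-event outcome, where the same mechanism operates. The protocol's sample size of 105 pairs is sound for the effect it states, and detection of deaths is not affected.

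**What to change.** 1. In 1.1, 3.1 and 5.5, define the outcome as *EMS-attended non-fatal overdose*, for both the 60-day rate and the time to subsequent overdose. In 4.4, state what the health department data contain and whether they capture overdoses with no EMS call. If they do, adapt the definition.
2. Limit the conclusion for this outcome to EMS-attended overdose.
3. Commit to a tipping-point analysis for both outcomes and for whichever Aim 1 designs are used: report the excess share f of unrecorded AR2-arm overdoses that would explain away an observed reduction, and the f at which the confidence limit reaches no effect. The details can sit in the statistical analysis plan.
4. Results within the AR2 arm by naloxone dispensed, which is already recorded (3.1, Aim 3, item b), may be shown as descriptive only. Item c of that aim notes that patients differ in receptivity, so recipients and non-recipients are not comparable.
5. Report deaths alongside, but do not let a fall in deaths stand as evidence that the AR2 reduces overdose frequency.

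The cost is wording in a few sections and one small analysis on data already collected. The downside is a narrower claim for this outcome.
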